**Figure 1. F1:**
[figure not shown]
Sentinel Wireframes showing (A) Sentinel asking the user to answer a question to begin determining their “persona*”*; (B) commencement of a tailored program for the user; and (C) one piece of content within the app.

**Table 1. T1:** Categories of Sentinel’s modules*.*

Category	Description	Modules, n	Pieces of content, n
Increasing knowledge of trauma and traumatic stress	Provides psychoeducation on primary and secondary trauma and stress	3	7
Increasing knowledge of posttraumatic growth	Provides psychoeducation on posttraumatic growth and an exercise to foster optimism	3	5
Increasing mind-body and emotional state awareness	Provides exercises to bolster awareness of body state and emotions	12	60
Learning strategies to cope with present distress	Provides self-help and problem-solving strategies to cope with stressors	18	88
Improving general mood and affect	Provides short exercises to improve mood and affect	10	39
Improving sleep	Provides psychoeducation on sleep and strategies to improve sleep	5	16
Improving social connectedness	Provides a strategy to increase and strengthen user’s social connections	1	3
Increasing levels of physical activity	Provides aerobic, strength, endurance, and resistance exercises to promote physical activity	4	67
Reducing levels of sedentary behavior	Provides psychoeducation on sedentary behavior, tips to reduce it, and short exercises	5	9
Increasing resilience	Provides an exercise to increase resilience to future traumatic events	1	3

The articles retrieved (from March 2004 to February 2024) were identified through a search over a 20-year period. In the first round of the search, additional references were identified by a manual search among the cited references. This included evidence-based therapeutic textbooks relevant to the treatment of trauma. With a review of current evidence [27,56,57], policy [58], theory [59-61], clinical guidelines [62,63], and experts by experience in stage 1 (FRs), a total of 297 pieces of content were generated, spread across 62 modules (see Figure 1C for an example piece of content). Module content drew upon cognitive behavioral techniques focused on changing maladaptive thoughts, behaviors, and coping strategies; mindfulness and spirituality to enhance stress management and maintain overall well-being; and approaches to develop skills in physiological regulation and social engagement, informed by Polyvagal Theory [64-67].

Integrating such approaches provides a comprehensive framework for addressing the complex and multifaceted nature of trauma, promoting holistic healing [68]. Sentinel adopts a strengths-based and deshaming approach to dealing with trauma, emphasizing the importance of resilience, positive attributes, and the facilitation of posttraumatic growth [36,69]. The aim is to empower FRs, thereby fostering recovery and personal development beyond trauma [70]. Accessibility rules were set in place to ensure content was clear and easily digestible. Specifically, each piece of content aimed to be no longer than 500 characters and to have good readability. Readability was tested using the Hemingway Editor, where “good” readability was considered a score of 9 or below. In addition, all the content was independently reviewed to check readability, as well as fidelity to the evidence base. A taxonomy was created to describe each module better. This included information on category (what does the module focus on; eg, mental health literacy and coping), type (what does the module specifically focus on within the category; eg, providing psychoeducation and teaching a self-help coping strategy), method (how can the content be engaged with; eg, imagery, writing, using senses, meditation, breathing, and an activity), targets (what “persona(s)” will benefit from the module), symptom (what problem(s) does the module aim to tackle), notification (whether the user receives notifications related to the module), and notification type (what does the notification ask of the user; eg, learn more about a topic and engage in an exercise). The modules are classified into 13 different categories, each informed by the themes gathered in stage 1 (Figure 2). The third step was to design how content would be delivered to the user. Sentinel is a personalized DI, as it will ask users which goals they would like to prioritize (eg, “feel less anxious” or “reduce stress”) and modify content in line with this. It also adapts content according to a number of person-specific characteristics, including work environment and content preferences (ie, what content the user likes or does not like to engage with). Hence, it will take the user’s individual circumstances and preferences into consideration when tailoring its content.

**Figure 2. F2:**
[figure not shown]
Interview themes informing content generation*.*

Across the user’s journey, Sentinel will also ask a series of questions to allow it to determine which content users should be given to help deal with common problems associated with traumatic stress. For example, the user may be asked if they experience difficulties falling and staying asleep or recurring nightmares and may be given sleep-related content depending on their answer. The app uses push notifications and reminders to increase and maintain user engagement [71]. These notifications are delivered at regular intervals and are designed to boost FRs’ overall engagement and well-being. Notifications also serve to reassess traumatic stress symptoms and maintain an adaptive, personalized management approach. It is, therefore, possible for a user’s “persona” to change as they use Sentinel.

### Phase 3: User-Informed Prototype Refinement

Informed by the outcomes of phases 1 and 2, our next steps will involve initial testing of the prototype for the Sentinel DI. We will conduct 3 co-creation video call sessions with FRs using Teams and simulations of notice boards or Post-its, and this will be complemented by collective discussions. The time immediately after our co-creation meetings will be dedicated to our development “sprints” to refine the Sentinel app. We have used this process previously in the development of DIs [72,73]. The first co-creation session will present the principles of the DI and then demonstrate and critique a simple initial application prototype. The second co-creation session will review the feedback from meeting 1 and progress during the next design sprint. The third co-creation session will review and finalize the DI design in preparation for the pilot or feasibility study. If a participant cannot attend a group meeting, one-to-one calls will be offered as an alternative. We will recruit participants initially using convenience sampling, followed by snowballing (connections with FR groups and previous survey or interview participants). We will aim to identify 6 to 8 participants for the co-creation groups to maximize the depth of conversation achievable with our discussions [74]. We will aim to include participants representing multistakeholder views across a variety of FR groups, including fire and emergency, paramedics, police, and frontline health and social care workers. Inclusion criteria will include participants aged 18 years and older and interested in contributing to current knowledge of DIs for trauma management in FRs. Ahead of developing the initial minimum viable product of the DI, we created a high-fidelity clickable prototype using a web app mock-up tool (Figma) that is used to gain user insights (phase 3). The prototype allows us to test the basic operation of the DI on various devices with diverse FR user groups (N=100), thereby simulating the user experience of the DI before the intensive app development phase commences [75]. The prototype includes a sample content module, simulated mood reporting and journaling, as well as detailed navigation and functional elements. We have also created an online link to the prototype and a short survey, which will allow us to gather views regarding design, content, and relevance of the DI as well as suggestions for improvements from a larger and more diverse group of potential users.

Co-creation sessions will be guided by structured prompts focusing on perceived relevance and credibility of content, emotional safety, usability and navigation, clarity of language, and appropriateness of personalization and notifications. Participants will be asked what aspects of the prototype feel most and least helpful, whether any content may be distressing or unhelpful, and how the app could better fit the realities of FR work. Feedback will be collated across sessions and reviewed by the multidisciplinary team, with priorities for change agreed upon during postsession debriefs and implemented through iterative development sprints to refine content, functionality, and user flow ahead of pilot testing.

### Phase 4: Pilot and Feasibility Testing of Sentinel

The final phase will involve assessing the feasibility and acceptability of Sentinel and exploring participants’ experiences of using the DI, with quantitative and qualitative data to be collected. Approval to commence with piloting has been obtained from the University Ethics Committee (REF UEC22/92). All data will be stored on secure servers, in line with appropriate security and compliance standards. The data stored are relevant to the functioning of the app and delivery of relevant personalized experiences. This will comply with General Data Protection Regulation and any relevant institutional data governance policies and meet industry standards for information and data security.

### Participants

We aim to pilot test the Sentinel digital app with a target sample of 100 FRs across diverse FR organizations. Participants who report distress associated with exposure to work-related traumas will be recruited from the National Health Service and FR organizations in the United Kingdom. Participants will be recruited through opportunity sampling via online posters distributed within FR organizations, emails sent directly to FR staff members, work intranet bulletin board advertisements, and targeted social media platforms. Interested participants will be eligible if they meet the following criteria: (1) aged 18 years or older, (2) being employed full-time or part-time at the National Health Service and/or an FR organization, (3) understanding the requirements of the study, and (4) having no major mental illness that may impact their capacity to consent to the trial. Given that the focus of the testing phase is to explore the feasibility, acceptability, safety, and usability of the DI, the sample size (N=100) is based on having sufficient variance to examine the feasibility for a larger study across a diverse population [76]. As this study is a feasibility pilot, it is not powered to detect statistically significant pre-post effects. The sample size (N=100) is based on recommendations for feasibility studies to estimate recruitment, retention, acceptability, and variance of outcome measures, which will inform sample size calculations for a future fully powered trial. Quantitative analyses will therefore focus on descriptive statistics, completeness of data, and estimation of effect sizes with CIs rather than hypothesis testing. The nonrandomized design was selected as appropriate for this feasibility study, which prioritizes assessment of acceptability, engagement, usability, and implementation rather than effectiveness. Feasibility will be judged using predefined progression indicators, including successful recruitment within the planned time frame, acceptable retention at follow-up, meaningful engagement with the app over the 6-week period, and satisfactory usability ratings, to inform the design of a future randomized controlled trial. All participants will receive the Sentinel app for 6 weeks. Notifications will encourage FRs to use the app, which is designed to be used in a stand-alone manner alongside routine care.

### Procedure

Participants will first be asked to provide informed consent and then complete an online Qualtrics questionnaire including the trial outcome measures. Following completion of the preintervention online questionnaire, participants will be provided with access to Sentinel and instructed to use the app for a 6-week period. Following the 6-week intervention period, participants will complete an online postintervention questionnaire. As well as looking at differences in pre- and post-intervention outcomes among FRs, the possibility that there might be some variations across different types of FRs with respect to responsiveness to the intervention will be explored. Furthermore, a series of open-ended questions will be asked concerning participants’ views on whether the Sentinel DI had worked for them and how it has impacted their mental health and well-being. An additional subset of FR participants (n=30) will then be asked to take part in an audio-recorded, one-to-one semistructured interview to gain a more in-depth understanding of their experiences of using Sentinel. Furthermore, health care professionals and service managers who referred FRs to the trial (n=20) will be interviewed to explore the acceptability and usability of Sentinel. Participants will be selected according to a sampling framework to capture varied demographics, experiences of work-based trauma, and levels of engagement with the Sentinel app. We will explain to all potential participants that participation is voluntary and that they can withdraw their consent at any point during the study without providing a reason. It will be made clear to FRs that, as the intervention does not replace standard care (but is provided in addition to it), withdrawal from the intervention will not impact their ability to continue to access standard care within the referring service or other sources of support they might access contemporaneously.

All participant data, including sensitive mental health information, are stored on secure, encrypted servers in accordance with General Data Protection Regulation and institutional data governance requirements. Data are pseudonymized at the point of collection, with identifying information stored separately and accessible only to authorized members of the research team. Sentinel does not share individual-level data with employers or third parties, and no identifiable app use, journaling, or symptom data are accessible to organizations. Data are retained only for the duration necessary to meet the study objectives and regulatory requirements, after which they will be securely deleted. Participants are informed of these safeguards during consent to ensure transparency and trust.

### Outcome Measures

To allow a comprehensive evaluation of the effectiveness of the Sentinel digital app in a future randomized controlled trial, we will work with stakeholders and subject experts to determine relevant outcome measures and then test the feasibility of their inclusion within this pilot study. This approach will also enable us to report an indication of effect and provide data to support sample size calculations for future studies. Potential metrics include employee well-being indices, rates of absenteeism and presenteeism, and overall organizational productivity. We will explore the integration of Sentinel with current organizational systems, particularly human resource platforms, which is essential for seamless implementation. We will assess the feasibility of such integration to ensure that Sentinel complements existing processes and enhances user engagement. Understanding the challenges and motivations that organizations face in evaluating the impact of DIs is vital. Factors such as data privacy concerns, resource allocation, and the need for stakeholder buy-in will be considered. By engaging with stakeholders, we aim to identify and address these challenges, ensuring a comprehensive evaluation strategy. This collaborative effort will guide the development of the outcome measures for our pilot trial, ensuring they are relevant, comprehensive, and aligned with organizational priorities. By involving stakeholders in this process, we aim to create a robust framework for assessing Sentinel’s impact, facilitating its successful implementation and adoption within organizations.

As primary outcomes, we will collect information on the total number of participants recruited and retained at different time points, including consent completed, app download, app use over 6 weeks, and follow-up questionnaire completion. We will also collect demographic information, including gender, age, ethnicity, health status, working status, family status, and occupation and recruitment setting. Other proposed psychometric outcome measures to be considered as secondary outcomes include the *Abbreviated Post-Traumatic Stress Disorder Checklist–Civilian* used to measure self-reported trauma symptoms [77]; the *Warwick-Edinburgh Wellbeing Scale* [78]; the *Burnout Measure–Short Version* [79]; the *Depression, Anxiety, and Stress Scale* [80]; the *Neuroception of Psychological Safety* [81]; the *Utrecht Work Engagement Scale* [82]; the *Mobile App Rating Scale* [83]; the *Post-Traumatic Growth Short Form* [84]*;* the *International Physical Activity Questionnaire Short Version* [85]; and the *WHOQOL-BREF* [86]. The validity and reliability of all questionnaires have been well tested [87-89]. More details on the proposed outcome measures have been provided in Table S1 in Multimedia Appendix 1. We also envisage including some physiological outcomes and remote monitoring in a subgroup, and the details of this will be explored during our earlier phases. Following pilot testing, further technology-based adjustments, in addition to delivery components, may require revisions.

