### Data Analysis

As this is a nonrandomized feasibility study, analyses will focus on describing recruitment, retention, engagement, usability, and safety outcomes rather than testing intervention effectiveness. Feasibility outcomes will be summarized using descriptive statistics, including counts and proportions for recruitment, retention, app download, completion of follow-up measures, and engagement with Sentinel over the 6-week period, with usability and acceptability measures will be reported using means, SDs, medians, and ranges as appropriate. Exploratory pre-post outcomes will be examined descriptively to inform the design of a future fully powered trial, with standardized mean differences (eg, Cohen *d*) and 95% CIs reported for changes in psychometric measures between baseline and follow-up; no formal hypothesis testing will be undertaken. Missing data will be assessed by reporting the extent and patterns of missingness across measures and time points, with no imputation performed, given the feasibility focus of the study. Exploratory subgroup analyses (eg, by FR role or level of engagement) will be conducted using stratified descriptive summaries only and interpreted cautiously to generate hypotheses and inform future trial design rather than to support inferential comparisons. Qualitative interview data will be analyzed using reflexive thematic analysis, with integration of quantitative and qualitative findings used to inform refinement of the intervention and trial procedures.

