## Results

Our pilot testing began in August 2025 and is planned for completion by August 2026. We anticipate a high attrition rate and will therefore recruit over a full year from several FR organizations using multiple recruitment methods, including organization newsletters and emails, target group presentations, and engagement of key stakeholders within organizations. As of January 16, 2026, a total of 119 participants have completed the initial survey, and 59 have downloaded the Sentinel app, with 24 having used the app for 6 weeks and completed the follow-up survey. Of this group, 13 participants have consented to an interview. We are therefore on track to meet our target recruitment sample.

Once data collection is complete, we expect to report results on the number of eligible FR participants consenting and the total number recruited and retained at different time points, including consent completed, app download, app use over 6 weeks, and follow-up questionnaire completion. We will also report on information about recruitment setting to inform the sampling strategy of a future randomized trial; completeness of outcome measures, including psychometric questionnaires and an indication of effect; attrition rates and reasons for withdrawal; the range of FR organizations offered Sentinel; participant completion rates for Sentinel; Sentinel platform use and engagement analytics; and safety of the Sentinel app and our trial procedures. We also expect to report on perceived barriers and enablers to integration and uptake into existing mental health care provider pathways. Exploratory analyses will be conducted to examine potential variation in intervention responsiveness across different FR groups. Given the feasibility focus and anticipated sample sizes within subgroups, these analyses will be descriptive and exploratory in nature, using stratified summaries and estimation of pre-post change scores by responder group rather than formal hypothesis testing. Findings will be used to inform subgroup specification and analytic strategies for a future fully powered trial.

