
### Limitations

As this protocol is for a pilot study, we are unable to conclude whether the Sentinel intervention will bring about any clinically significant change after intervention. However, this study design, with its focus on feasibility, acceptability, safety, and usability, will provide valuable insights that will inform parameters for a future randomized trial, should this be indicated. The inclusion of organizationally led impact outcomes, psychometric measures, and open-ended questions asking FR users whether the DI worked for them and how it had impacted their mental health and well-being will provide some preliminary evidence of its efficacy. Moreover, feedback from multiple stakeholders, including those who refer FRs to the feasibility trial, will allow for improvements in the Sentinel app, trial procedures, and plans for implementation. In our work, to date, we have not yet engaged with military FRs and/or family members of FRs; we would view this as a priority in our next steps in DI development, given their central role in providing social and/or familial support to FRs [99]. This aligns with emerging work on persistent traumatic stress exposure [100], which highlights the importance of considering ongoing and cumulative trauma within relational and support systems.

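### An uncontrolled pilot is said to give an indication of effect and preliminary evidence of efficacy, which its design cannot provide

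*Protocol article*

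**What the plan says.** Phase 4 is a single-group study. Under Participants: "All participants will receive the Sentinel app for 6 weeks", and the app is "designed to be used in a stand-alone manner alongside routine care". On who enters: "Participants who report distress associated with exposure to work-related traumas will be recruited".

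Three places attach an effect reading to this design.

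- Outcome Measures: "This approach will also enable us to report an indication of effect and provide data to support sample size calculations for future studies".
- Results lists an indication of effect again among the findings to be reported.
- Limitations says that organizational outcomes, psychometric measures and open-ended questions together "will provide some preliminary evidence of its efficacy".

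Other places point the other way. Data Analysis says that "analyses will focus on describing recruitment, retention, engagement, usability, and safety outcomes rather than testing intervention effectiveness". It plans standardized mean differences (Cohen d is the example) with 95% CIs for baseline-to-follow-up change, without hypothesis tests and without imputation, to inform the design of a later powered trial. Participants says the study is not powered for pre-post effects. It also says that "The sample size (N=100) is based on recommendations for feasibility studies", and names recruitment, retention, acceptability and outcome variance as the quantities to be estimated for the later sample size. Limitations says that no conclusion on clinically significant change will be possible.

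**The concern.** A before-after change in one group is not an estimate of what the app does. Four other sources of change are built into this design:

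- people enter when distressed, so scores may regress to the mean;
- they may recover naturally over 6 weeks;
- other care continues;
- without imputation, only those who return the follow-up questionnaire contribute a change score.

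The open-ended question on whether the app worked, and any organizational outcomes, are uncontrolled in the same way.

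Two things are at stake. First, a favourable pre-post d could be published and read as early evidence that the app works. Second, the same d could be carried into the planned randomized trial as its target difference. That trial needs a between-group difference, and a within-person change that includes non-treatment improvement would make it too small.

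**Working it through.** **1. The plan's own figure.** The target of 100 comes with no alpha, power, effect size, SD or precision target, so there is no calculation to reproduce. Everything below is illustration.

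**2. Statements side by side.** Data Analysis excludes testing effectiveness. Outcome Measures and Results promise an indication of effect. Limitations rules out a conclusion on clinically significant change and, two sentences later, claims preliminary efficacy evidence. The article never names regression to the mean, natural recovery, concurrent care or selective drop-out as limits on the pre-post change.

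**3. Regression to the mean with an inert app.** The article gives neither a test-retest correlation r nor a distress cut-off. Assume r = 0.6 to 0.9 and entry above c SD on the measured score. The expected fall, in population SD units, is (1 − r) × φ(c)/(1 − Φ(c)).

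- c = 0: the ratio is 0.399/0.500 = 0.798, so the fall is 0.1 × 0.798 = 0.08 to 0.4 × 0.798 = 0.32.
- c = 0.5: the ratio is 0.352/0.309 = 1.14, so the fall is 0.1 × 1.14 = 0.11 to 0.4 × 1.14 = 0.46.

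**4. Completers.** From the Results section, at 16 January 2026: 59/119 = 50% had downloaded the app and 24/119 = 20% had completed follow-up (24/59 = 41% of downloaders). These are interim figures, since some participants may not yet have reached week 6. The article itself expects high attrition.

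**5. What the confidence interval covers.** With SE(d) = √(2(1 − r)/n + d²/(2n)), d = 0.3 and r from 0.8 down to 0.5, the 95% half-width is 0.27 to 0.41 at n = 24 and 0.13 to 0.20 at n = 100. A larger n narrows the interval but leaves the bias in step 3 unchanged.

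**6. If d became the target difference.** Assume two arms, 80% power and two-sided 5%, with n per arm = 2(1.960 + 0.842)²/d².

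- For d = 0.5 this is 2 × 7.85/0.25 = 62.8, or 64 with the t distribution.
- With 64 per arm, power is about 39% at a true between-group d of 0.3 and 20% at 0.2.
- The numbers needed (t distribution) are 176 and 394 per arm.

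The same by amount of non-treatment change (normal approximation):

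| True d | Non-treatment change | Pre-post d | n per arm chosen | n per arm needed | Actual power |
|---|---|---|---|---|---|
| 0.2 | 0.1 | 0.3 | 175 | 393 | 46% |
| 0.2 | 0.2 | 0.4 | 99 | 393 | 29% |
| 0.2 | 0.3 | 0.5 | 63 | 393 | 20% |
| 0.3 | 0.1 | 0.4 | 99 | 175 | 56% |
| 0.3 | 0.2 | 0.5 | 63 | 175 | 39% |
| 0.3 | 0.3 | 0.6 | 44 | 175 | 29% |

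**7. What one arm can supply.** By the chi-square interval, the 95% CI for an SD runs from 0.88 to 1.16 times the estimate at n = 100, and from 0.78 to 1.40 times at n = 24. Retention and completeness can also be estimated directly.

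**The case against.** The article is cautious in several places. Its primary outcomes are recruitment and retention counts. It says that it is not powered for pre-post effects, tests no hypotheses, reads subgroups cautiously and cannot conclude on clinical change. These caveats are genuine, but they concern random error and clinical significance. They do not tell a reader that the estimate is biased as a measure of the app's effect, however large the sample.

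A reader might infer that the article plans to use the pre-post change as the effect size for the next trial. It does not say so. Participants names variance, retention and related quantities, which one arm can properly estimate. What remains is that Outcome Measures joins the effect indication and sample-size data in one sentence, and Data Analysis offers the pre-post results to inform the later design. That use is left open.

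A reader might also infer that an inert app would be sure to show improvement. That goes too far. Distress appears in the recruitment sentence but not among the four numbered eligibility criteria, and no scale or cut-off is given. If people with persistent distress volunteer, regression could be much smaller than in step 3. Several of the proposed scales, such as those for physical activity and work engagement, do not measure distress at all.

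Nor can one infer that the organizational outcomes cited in Limitations do not exist. Outcome Measures names candidates, and the appendix table is not shown.

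On subgroups, the article says: "Exploratory analyses will be conducted to examine potential variation in intervention responsiveness across different FR groups". Its next sentences define this as descriptive pre-post change scores, so that wording is a minor matter.

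**Conclusion.** The point stands as one of moderate severity. The article claims an indication of effect and preliminary efficacy evidence from outcomes that are all uncontrolled, against its own statement in Data Analysis. This rests on the text and the design and needs no assumption.

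The size of the bias is unknown. The 0.08 to 0.46 SD range depends on an assumed r and entry level and on selection acting through the measured score. The loss of power (39% or 20% instead of 80%) is conditional: it arises only if a pre-post d of about 0.5 is taken as the target difference and the true effect is 0.3 or 0.2. None of those values is in the article.

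**What to change.** - **Outcome Measures and Results:** replace the promise of an indication of effect with *pre-post change, not attributable to the app*.
- **Limitations:** delete the efficacy phrase. Name regression to the mean, natural recovery, concurrent care and completer selection as limits on the pre-post change.
- **Data Analysis:** state that the pre-post d will not be used as the target difference. Only SDs, the baseline/follow-up correlation, retention and completeness will feed the next sample size. The target difference will be set independently, for example as a minimum important difference.
- **Optional:** in Procedure and Results, write *pre-post change* instead of responsiveness to the intervention.

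These are changes of wording and reporting. No procedure, outcome or sample size alters, and they can still be made because pilot testing is planned to run to August 2026. The cost is a more modest claim.
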